# ERGOGENIC EFFECTS OF CREATINE SUPPLEMENTATION

# CHR PROTOCOL H-1080-16219

**STUDY AIM AND PURPOSE:**

_ To test the hypothesis that short-term administration of creatine monohydrate improves skeletal muscle mass and strength, as well as muscle metabolic and performance responses to exercise, in patients with HIV infection.

_ To test the hypothesis that chronic administration of creatine augments the functional benefits of progressive resistance training related to skeletal muscle mass and strength, as well as muscle metabolic and performance responses to exercise.

_ To evaluate the effects of creatine on systemic metabolic, immunologic, and virologic parameters.

**2. BACKGROUND**

As the focus of HIV management shifts from acute to long-term care, loss of lean body mass (LBM), in particular skeletal muscle, is emerging as one of the most disabling aspects of chronic HIV infection. Although progressive resistance exercise has been associated with marked improvements in weight, LBM, and strength in subjects with HIV infection (1-4), initiating and adhering to an exercise regimen that is sufficiently strenuous to result in these improvements is difficult. Creatine monophosphate, which is marketed as a dietary supplement, has gained popularity in the HIV community, as well as the athletic community as a whole, on the basis of widespread belief that it can enhance athletic performance (5,6). Anecdotal reports suggesting that increases in strength, endurance, and muscle mass are associated with creatine supplementation have motivated individuals to return to the gym and adhere to fitness programs they might have otherwise abandoned (6,7). These reports indicate that trainers and coaches, in particular, have commented favorably on creatine’s apparent potency and positive impact on adherence to exercise regimens.

Creatine (N-[aminoiminomethyl]-N-methyl glycine) isfound primarily in skeletal muscle, where it exists in both a free and phosphorylated form, phosphocreatine (PCr). Phosphocreatine is an important energy source in muscle, by virtue of the transfer of its phosphate group to adenosine diphosphate (ADP) to form adenosine triphosphate (ATP), a reaction that is catalyzed by the enyzme creatine kinase. This process of energy regeneration is particularly important during short duration high-intensity physical activity, as ATP is the source of energy for muscle contraction, and intramuscular stores of ATP are limited. Creatine supplementation in healthy subjects has been shown to increase total body mass (8-10), although these findings may reflect water retention. Unfortunately, only a small number of studies have been performed to look at the effect of creatine together with exercise training on LBM (8-12). Although some of these studies suggest that creatine therapy increases LBM, concomitant changes in hydration status may also have affected these results. Further studies are needed to determine the precise effect of chronic creatine supplementation together with exercise training on LBM and to evaluate whether measured increases in LBM reflect increased functional tissue or merely increased hydration of LBM.

While the effects of creatine supplementation in healthy subjects are unclear, studies of populations with initial deficits in muscle function generally indicate a beneficial effect. For example, the effects of creatine supplementation on PCr availability and resynthesis rates appear to be greater in older subjects (13). Subjects with mitochondrial cytopathies exhibited an 11% increase in performance during non-ischemic dorsiflexion exercise following 3 weeks of creatine supplementation (14). Ten days of creatine supplementation in subjects with chronic heart failure resulted in a 12% increase in muscle [PCr] (by biopsy) and significant increases in 1- and 2-legged exercise performance (15).

1. **SIGNIFICANCE**

Increased PCr availability and improved physical exercise performance with creatine supplementation form the basis for creatine use as an ergogenic aid in the community. However, the scientific evidence for its efficacy has not been clearly established. Not all studies demonstrate a positive effect of creatine supplementation, and careful randomized placebo-controlled studies are necessary to evaluate its safety and efficacy.

As concern about potential metabolic toxicities of highly active antiretroviral therapy (HAART) mounts, there is increasing interest in nonpharmacologic approaches to management of the metabolic complications of HIV infection and its therapies. Because resistance exercise is known to improve insulin resistance and lipid profiles and reduce abdominal fat, in addition to increasing muscle mass, patients in the current treatment era are frequently encouraged to undertake such training. Laboratory studies consistently demonstrate the positive effects of exercise, but a remaining challenge is to identify ways of encouraging patients to not only initiate but also adhere to an exercise regimen. If creatine supplementation can help in this latter effort, it could be a useful nonpharmacologic means of assisting with efforts to not only increase muscle mass but also manage the modern metabolic complications of HIV infection.

1. **METHODS**

**A. General Study Design:** This is a randomized, placebo-controlled study to evaluate the effect of creatine supplementation on skeletal muscle size and function (i.e., strength, energy metabolism, work capacity, fatigue); whole-body exercise performance; body composition; systemic metabolic parameters; immune function; and viral replication. This study is also designed to determine whether creatine supplementation augments the functional benefit derived from progressive resistance exercise. Forty HIV+ subjects will be randomly assigned, on a 1:1 basis, to receive creatine monohydrate or placebo for a period of 14 days, followed by a 12-week program of progressive resistance exercise training during which administration of creatine monohydrate or placebo will continue.

**B. Methods of Data Analysis:** Sample size calculations and methods of data analysis were prepared in consultation with [name], biostatistician for the General Clinical Research Center (GCRC) at San Francisco General Hospital (SFGH). Intent-to-treat analyses will include all subjects who provide outcome data. Within each group, the one-sample t-test will be used for change measures that appear to be normally distributed, and the Wilcoxon signed-rank test will be used otherwise. Comparisons between the creatine and placebo groups will be by two-sample t-test or by Wilcoxon rank-sum test.

**C. Subject Selection:**

**1. Who and why:** HIV-positive adults who are currently clinically stable will be recruited for study. We anticipate that such individuals will be able to engage in a sufficiently rigorous exercise training regimen to enable us to determine whether creatine supplementation is an effective ergogenic aid.

**2. Total number:**  A sample size of 20 per group will allow for detection of standardized effect size of 0.9 with 80% power.

**3. Inclusion criteria**: HIV-positive subjects must be on optimized antiretroviral regimens, as determined by their primary medical providers, and plan to remain so during the study. Men and women on hormone replacement therapy and women using hormonal contraceptives must have been on stable regimens for the preceding 6 months and plan to continue on such treatment throughout the study period.

**4. Exclusion criteria:** Serum creatinine > 1.5 mg/dl or clinical evidence of renal disease or prior kidney transplant; creatine kinase (CK) > 1.5 times the upper limit of normal (ULN); hemoglobin < 8.5 g/dl; AST, ALT, or LDH ³5 X ULN;uncontrolled diarrhea (>6 stools per day); impaired oral intake; persistent nausea or vomiting; untreated hypogonadism; pharmacologic use of growth hormone, testosterone, oxandrolone, nandrolone decanoate, oxymetholone, or other oral, injectable, or transdermal anabolic steroids, androstenedione, or dehydroepiandrosterone (DHEA) within the preceding 6 months (subjects with documented hypogonadism on stable testosterone replacement, defined as a dose <300 mg q2 weeks for the preceding 6 months, will be allowed to enroll); use of glucocorticoids, megestrol acetate, creatine monohydrate, cytokine inhibitors (thalidomide, pentoxifylline, ketotifen), drugs known to adversely affect renal function, cytokines, parenteral or tube feeding, or initiation of treatment for a systemic infection within 30 days prior to enrollment; history of angina, coronary heart disease, or congestive heart failure; current pregnancy or lactation or plans to become pregnant. Because vegetarians are known to have lower intramuscular concentrations of creatineand therefore may experience a much greater relative increase in muscle creatine levels, we will exclude such individuals from this study.

**D. Subject Recruitment:** Recruitment will be by advertisement, ongoing interaction with local physicians and AIDS organizations such as the Community Consortium, and word of mouth.

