**5. Venipuncture:** Venipuncture and placement of intravenous lines may result in a hematoma, which can be painful but carries no significant risks. Infections from IV lines rarely occur from such brief placements. However, any signs of inflammation will lead to removal of the catheter and treatment with heat and elevation.

**6. Phlebotomy:** The total amount of blood drawn will not exceed 200 cc.

**H. Treatment and Compensation for Injury:** If a subject is injured as a result of being in this study, treatment will be available. The cost of such treatment may be covered by the University of California. Subjects will be informed that they may obtain further information by calling the Committee on Human Research.

**I. Alternatives:** Subjects may choose not to participate in the study.

**J. Costs to the Subject:** There will be no charges to the subject. The costs of the study medication and all tests required for the study will be covered by the study. Transportation costs to and from the VAMC will also be reimbursed or covered by taxi vouchers.

**K. Reimbursement of Subjects:** Subjects will be reimbursed $1,000 for completing the study. Subjects who do not complete the full study will be reimbursed $200 for each major assessment (baseline and week 2).

**L. Confidentiality of Records:** Participation in research may involve loss of privacy. The subjects' research records will be handled as confidentially as is possible within the law. All records will be coded and stored in the office of the PI. Copies of the signed consent forms are kept by the GCRC, the subjects, and the PI. Copies of the subjects’ medical records may be reviewed by representatives of the Food and Drug Administration. No individual identities will be used in any reports or publications resulting from this investigation.

**5. QUALIFICATIONS OF INVESTIGATORS:** Over the past six years, Drs. [name] and [name] have conducted numerous studies of anabolic and anticytokine therapies and their metabolic effects in HIV-infected individuals with weight loss, as well as studies of body composition and energy metabolism in groups of men and women with HIV infection. [name] has performed numerous studies of muscle metabolism and function in subjects with a variety of chronic catabolic conditions or neuromuscular disorders.

**6. BIBLIOGRAPHY:** attached.

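### The stated 80% power at 0.9 SD holds for 20 analysed per group, but 20 per group is also the number randomised, so any missing week-14 data takes power below the stated figure

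*Protocol*

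**What the plan says.** Section C (Subject Selection), item 2 (Total number), gives the whole sample-size justification in one sentence: "A sample size of 20 per group will allow for detection of standardized effect size of 0.9 with 80% power". It states no significance level or sidedness, and does not say whether the 20 are randomised or analysed.

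Section A (General Study Design) fixes the number randomised: "Forty HIV+ subjects will be randomly assigned, on a 1:1 basis, to receive creatine monohydrate or placebo". That is 20 per group.

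Section B (Methods of Data Analysis) fixes the analysis set: "Intent-to-treat analyses will include all subjects who provide outcome data". It also names the between-group tests: "Comparisons between the creatine and placebo groups will be by two-sample t-test or by Wilcoxon rank-sum test".

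Section K (Reimbursement of Subjects) provides for people who leave early: "Subjects who do not complete the full study will be reimbursed $200" for each major assessment, and it names those assessments as baseline and week 2. The final assessments come at week 14, after 12 weeks of training (section F, item 5g, Follow-up assessments). The protocol states no allowance for loss and no replacement of lost subjects.

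**The concern.** The number that the power statement needs in the analysis is the same as the number that enters the trial. A subject without outcome data leaves the analysis, and nothing makes up for that loss. The protocol expects that some subjects may stop early, because it sets a payment for them.

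The exposure is uneven. The first aim (short-term effect) is measured between days 12 and 14, when little loss has had time to build up. The second aim (whether creatine adds to the benefit of training) is measured at week 14. By then subjects have been asked for three supervised sessions a week for 12 weeks, and for repeat magnetic resonance testing that takes 3 to 4 hours. A subject who stops after week 2 counts for the first aim and not for the second, yet one power figure is given for both.

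At stake is how a non-significant week-14 result is described. Quoted against 0.9 SD with 80% power, it would suggest more sensitivity than the trial had if some subjects were missing.

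**Working it through.** **Inputs from the protocol.** Number per group n = 20 and standardised effect d = 0.9 with 80% power (section C, item 2); 40 randomised 1:1 (section A); two-sample t-test as the reference test, with analysis of those with outcome data (section B).

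**Assumptions.** Two-sided alpha of 0.05. Loss of 5% to 20%, equal in the two groups. The protocol gives neither.

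**Step 1: reproduce the plan's figure.** Normal approximation:

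n = 2(z₀.₉₇₅ + z₀.₈₀)² / d² = 2(1.960 + 0.842)² / 0.9² ≈ 15.70 / 0.81 ≈ 19.4, rounded up to 20 per group.

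Power at n = 20: Φ(d√(n/2) − 1.960) = Φ(0.9 × √10 − 1.960) = Φ(2.846 − 1.960) = Φ(0.886) = 81.2%.

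The exact calculation uses the noncentral t distribution with 2n − 2 = 38 degrees of freedom and noncentrality d√(n/2) = 2.846. It gives 79.2%. Both values agree with the stated 80% within rounding. By the exact calculation 21 per group is the first whole number above 80% (81.2%), so 20 leaves no slack.

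**Step 2: check the assumed level.** A one-sided 5% test would need only 16 per group by the normal approximation, and 20 per group would then give 87.5% (exact t). That does not match the protocol's sentence, so two-sided 5% is the consistent reading.

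**Step 3: apply loss to the 40 randomised.** Analysed per group = 20 × (1 − loss). Power is recomputed at d = 0.9. The last column is the d at which exact-t power equals 80%.

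| Assumed loss | Analysed per group | Noncentrality 0.9√(n/2) | Power, exact t | Power, normal approx. | Detectable d at 80% power |
| --- | --- | --- | --- | --- | --- |
| 0% | 20 | 2.846 | 79.2% | 81.2% | 0.91 |
| 5% | 19 | 2.774 | 77.0% | 79.2% | 0.93 |
| 10% | 18 | 2.700 | 74.6% | 77.0% | 0.96 |
| 15% | 17 | 2.624 | 72.1% | 74.7% | 0.99 |
| 20% | 16 | 2.546 | 69.3% | 72.1% | 1.02 |

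One loss per group costs about 2 points. From 10% loss the shortfall is clear under both formulas: at 10% it is 5.4 points below 80% by the exact t (80 − 74.6) and 3.0 by the normal approximation (80 − 77.0).

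**The case against.** The best defence is that the sentence contains no error. It says what 20 per group can detect, and that is correct. The protocol gives no loss rate. It offers $1,000 for completion and covers transport to the imaging site, both of which favour retention. With one loss per group the change is trivial. Even at 10% to 20% loss the detectable effect moves only from 0.91 to 0.96–1.02 SD, which is large in every case.

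Much of this stands. A reader might infer that the sample size was miscalculated or that the trial is bound to miss its stated power. The documents support neither: the figure is reproduced, and the shortfall depends on a loss whose size is unknown. The payment rule shows that non-completion is foreseen but not how much, and its week-2 payment means that some early leavers would still serve the first aim.

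Two further inferences also fail. Stopping study drug under Safety Monitoring is not loss of outcome data: those subjects continue to be followed, and section B keeps anyone with data. Nor does the option of a rank-sum test lower the stated power in any clear way. Section B pairs the t-test with normal-looking changes for the within-group tests, and the between-group sentence reads naturally the same way. A rank-sum penalty worked out for normal data would therefore apply where the t-test is used.

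What the defence does not answer is that the protocol itself fixes the number randomised, the analysis set and the power claim, and the three agree only at zero loss. A later analysis plan cannot restore subjects who were never enrolled.

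**Conclusion.** The point holds in a limited form. The power statement is correct within rounding for 20 analysed subjects per group and has no margin. Because 20 per group is also the number randomised, and subjects without outcome data are left out, loss takes power at 0.9 SD below the stated figure, chiefly at week 14. For assumed losses of 5% to 20%, power is 77% to 69% and the detectable difference is 0.93 to 1.02 SD.

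This rests on a two-sided 5% level (inferred because it reproduces the figure), equal loss in the two groups, and loss rates that are illustrations and not the sponsor's expectations. It is a matter of stating the trial's sensitivity correctly, and it is no case for calling the design invalid.

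**What to change.** Restate the sentence in section C, item 2, in evaluable subjects and give the significance level. For example:

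*20 evaluable subjects per group give 80% power (two-sided alpha 0.05) to detect a difference of about 0.91 SD. If 10–20% of the 40 randomised lack week-14 data (an assumption), the difference detectable with 80% power is about 0.96–1.02 SD.*

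Give separate figures for the week-2 and week-14 comparisons, because loss will differ between them. If the sponsor has its own estimate of retention, use that in place of the assumed range.

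The cost is a sentence or two of text and a less favourable figure. The fix adds no subjects and changes no procedure.

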#### **F. Experimental protocol:**

**1. Screening:** The assessment of eligibility will include a medical history targeted to HIV and cardiovascular disease; physical examination; exercise, weight, and antiretroviral history; electrocardiogram;current medication inventory; and nutritional assessment by 24-hour recall. Blood samples will be collected for standard chemistries and hematology to exclude subjects with any significant laboratory abnormality as listed above.

**2. Baseline assessments:** Eligible subjects will undergo baseline testing that includes measurements of muscle cross-sectional area and isometric strength, fatigue and metabolism; dynamic strength of knee and ankle flexors and extensors; habitual physical activity; and total and regional body composition. Blood samples will be collected for measurement of lipids and lipoproteins, glucoregulatory, gonadal, and adrenal hormones, viral load, and indices of immune function. Subjects will prepare a 3-day food intake diary to quantitate baseline energy and macronutrient intake and meat consumption.

**3. Randomization:** Subjects will then be randomized, in a 1:1 fashion, to receive either creatine or placebo, following the dosing regimen described below. Between the 12th and 14th day after randomization, subjects will repeat all of the measurements performed at baseline except for physical activity and food intake. All subjects will then begin a 12-week progressive resistance exercise program, consisting of 3 training sessions per week. Subjects will remain on their assigned oral study regimens (creatine or placebo) during these 12 weeks.

**4. Creatine Dosing:** Although current dosing regimens for creatine supplementation are known to vary widely in the community, we have selected a dosing regimen based on loading, maintenance, and rest cycles used by creatine manufacturers and experts in the use of creatine for athletic training. The loading dose is a total of 20 g pure creatine monohydrate or placebo in capsules, taken in four divided dosesdaily with a non-caffeinated solution containing 20 g of simple carbohydrate. This regimen will be followed for 5 consecutive days, after which subjects will begin maintenance dosing of 4.8 g daily. Maintenance dosing will continue for five weeks, after which this cycle of loading and maintenance will begin again.

**5. Procedures:** Unless noted otherwise, all procedures will be performed in the GCRC at SFGH.

*a) Habitual activity:*  Daily activity will be measured with a 3-dimensional accelerometer (16-18). Each subject will be instructed in the use of the monitor, and data will be acquired for 7 consecutive days. The monitor will be worn in a pack snugly fit around the waist during all waking hours, except time spent in bathing or swimming. Each subject will also keep a simple written record of physical activity for those 7 days.

*b) Muscle size and function:* Measurements of muscle function will be performed using magnetic resonance spectroscopy (MRS), and cross-sectional muscle area by magnetic resonance imaging (MRI), at the San Francisco VAMC. Maximal isometric contraction force (MVC) will be measured in the unfatigued dorsiflexor muscles of all subjects. Each subject will be placed in the leg exercise apparatus with the foot securely strapped to the force platform. The apparatus will then be loaded into the magnet, and the subject positioned comfortably in an upright position. Three MVCs lasting 3-4 seconds each will be performed, separated by 1 minute rest. Two exercise protocols will then be performed. The first, to assess the rate of PCr recovery (an index of oxidative capacity), will consist of a 15 sec MVC. The second exercise protocol, used to quantitate initial PCr hydrolysis rate, initial rate of fatigue, total work capacity and total fatigue, will consist of 60 consecutive MVC's, one every 2 seconds. Contractions will be paced using a pre-recorded cassette tape, and subjects will be given strong verbal encouragement throughout each exercise. Both protocols will be performed on the same day, with a 20 minute rest period between them.

Fat-free muscle and fat cross sectional areas (CSA) of the lower leg, quadriceps, and gluteal region will be determined using MRI (19). A total of 33 transverse slices will be acquired in an interleaved fashion (slice thickness = 4 mm, echo time = 14 ms, repetition time = 510 ms, flip angle = 70°, field of view = 210 mm, 256 X 256 matrix, 2 acquisitions). The slice in which the anterior compartment CSA is largest will then be analyzed for fat-free and fat-containing areas. Quadriceps and gluteal muscle and fat CSA will be measured in a similar fashion. Ten-millimeter thick image slices will be collected from the head of the femur to the knee joint. The slice with the largest muscle CSA and the two adjacent slices will be used for analysis, as described above. The time required to complete both the MRS and MRI testing is 3-4 hours.

*c) Body composition:* Whole-body and regional fat and lean body mass will be measured by dual-energy X-ray absorptiometry (DEXA). Subjects lie on a padded scanning table while wearing a standard hospital gown, underwear, and pajama bottoms that contain no snaps or other material that may interfere with attenuation. The procedure takes approximately 20 minutes for most subjects.

*d) Total body water* will be measured by deuterium oxide dilution. After collection of a baseline plasma sample, subjects will drink 10 g of deuterium oxide (99.9 atom %). The drinking vessel will be rinsed with three successive volumes of 20 ml each of tap water, such that the total fluid intake will be 70 ml. During the following three hours the subject will sit or rest, avoiding any strenuous activity. After three hours a second plasma sample will be collected.

*e) Anthropometry*: Waist, hip, neck, chest, thigh, and midarm circumferences; and subscapular, triceps, abdominal, and thigh skinfold thicknesses will be measured in triplicate by a trained dietitian (20).

*f) Resistance exercise training:* Following testing at the end of the baseline period (week 2), all subjects will begin 12 weeks of progressive resistance exercise training. Training will be performed under the guidance of an American College of Sports Medicine (ACSM) certified Exercise Specialist. Prior to starting any of the exercises, all subjects will warm up for 5 minutes on a cycle ergometer and all muscle groups to be exercised will be stretched 3 times for 20 seconds each. Initial muscle strength will be measured and peak isometric force and dynamic torque will be used to develop a program for training of the muscle groups. Dynamic training will begin with 2 sets of 10 repetitions at 70% 1 repetition maximum (RM), which is the maximum amount of weight that can be lifted through a joint’s range of motion, for the first 2 weeks, and then will progress to 2 sets of 10 repetitions at 85% 1RM for the next 10 weeks. All subjects will train 3 times per week, and each training session will be supervised. The protocols to be used are similar to those used in other strength training studies (21,22) and apply the principles of gradual progression, overload, and specificity of training known to be necessary to achieve muscle strength improvements (23-26). Subjects will be re-tested on the training equipment every 2 weeks to reassess maximal strength levels, and the training intensities will be adjusted to reflect any strength changes.

*g) Follow-up assessments:*After initiation of exercise training, subjects will undergo monthly assessment of weight, body composition by DEXA and anthropometry. Blood samples will also be collected at these visits for safety monitoring. At the end of the 12-week training period (week 14 of the study) subjects will repeat all of the assessments performed before initiation of exercise, including assessment of habitual physical activity and food intake.

###

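### Baseline means week 0 in most of the protocol but week 2 in the training section, and no reference visit is named for change, so the Aim 2 test could include the pre-training effect

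*Protocol*

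**What the plan says.** The Study Aim and Purpose section separates two hypotheses. Aim 1 concerns short-term creatine. Aim 2 is that "chronic administration of creatine augments the functional benefits of progressive resistance training".

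The visits are described as follows:

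- **Experimental protocol, items 2 and 3 (Baseline assessments; Randomization).** "Eligible subjects will undergo baseline testing that includes measurements of muscle cross-sectional area", among other measures. Randomization comes afterwards, and the visit on days 12 to 14 repeats most of those baseline measurements.
- **Section K (Reimbursement) and Attachment 2 (timetable).** Baseline and week 2 are separate assessments, with separate columns in the timetable.
- **Experimental protocol, item 5(f) (Resistance exercise training).** "Following testing at the end of the baseline period (week 2), all subjects will begin 12 weeks of progressive resistance exercise training".
- **Experimental protocol, item 5(g) (Follow-up assessments).** Week 14 repeats the pre-exercise assessments. That description fits both week 0 and week 2.

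Section B (Methods of Data Analysis) says that within each group the "one-sample t-test will be used for change measures" if they look normally distributed, with a signed-rank test otherwise. The arms are compared by two-sample t-test or rank-sum test. No reference visit for change is named for either aim.

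**The concern.** One word covers two different reference points: a visit before randomization and the end of a period on study drug. The ambiguity lies exactly where Aim 1 ends and Aim 2 begins. Change from week 0 to week 14 contains the short-term supplementation effect (Aim 1) plus anything that happens during training. Change from week 2 to week 14 removes whatever is already present at week 2. Two analysts could run different Aim 2 tests in good faith from the same text.

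If week 0 were used, an effect that arose before training and simply persisted could be reported as creatine enhancing the response to training. The protocol's background makes such an effect plausible. It cites a 12% rise in muscle phosphocreatine after ten days of creatine in heart failure, without any mention of training, and it says that gains in body mass in healthy subjects may be water.

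**Working it through.** **The plan's own figure.** Section C.2 states: "A sample size of 20 per group will allow for detection of standardized effect size of 0.9 with 80% power". Alpha and sidedness are not given; I assume two-sided 5%. By the normal approximation, n per arm = 2 × (1.960 + 0.842)² / 0.9² = 19.4, which rounds up to 20. The exact t calculation at n = 20 gives power 79.2%. The stated figure reproduces.

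**Scenario.** Creatine has an effect L in weeks 0 to 2 only. It persists unchanged to week 14, and creatine adds nothing during training. L is in SDs of the week 0 to 14 change. The protocol gives neither an SD nor an expected 14-day effect, so every value of L is an assumption.

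**Formula.** With n = 20 per arm, the two-sample t-test has 38 degrees of freedom, critical value 2.024 and noncentrality L × √(20/2) = 3.162 × L. The rejection probability is the two-tailed noncentral t probability.

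| Assumed L (SD) | Noncentrality | Week 0–14 test significant | Week 2–14 test significant |
|---|---|---|---|
| 0.1 | 0.32 | 6% | 5% |
| 0.25 | 0.79 | 12% | 5% |
| 0.5 | 1.58 | 34% | 5% |
| 0.9 | 2.85 | 79% | 5% |

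The last column is 5% by construction: a constant effect already present at week 2 cancels from the week 2 to 14 difference. The 79% is simply the trial's design power, because 0.9 SD is its target effect.

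**Price of the week 2 to 14 contrast.** Assume SDs of 1.0 for the week 0 to 14 change and 0.8 for the week 2 to 14 change (for example, independent changes with SDs 0.6 and 0.8, since √(0.36 + 0.64) = 1.0). Let the total effect be 0.9, half of it present by week 2.

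- Week 0 to 14: 0.9 / 1.0 = 0.90 SD, power 79%.
- Week 2 to 14: 0.45 / 0.8 = 0.56 SD, power 41%.

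**Data availability.** Attachment 2 schedules 1-repetition maximum, MRI, MRS, total body water, DEXA, anthropometry and the laboratory panels at weeks 0, 2 and 14. The accelerometer and food diaries are scheduled at weeks 0 and 14 only.

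**The case against.** The strongest reply is that the label in item 5(f) does no harm by itself. It sits in a procedures section and gives the week number, so nobody would test at the wrong time. Read literally, it makes week 2 the starting point for training and so points towards the week 2 to 14 change. Linking aims to visits is also commonly left to a SAP, which is not at hand.

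Much of this stands. A reader might infer that the protocol plans to test Aim 2 from week 0, or that false claims of augmentation are to be expected. The documents support neither: no reference visit is chosen, and for small early effects (0.1 to 0.25 SD) the rate is only 6% to 12%. A reader might also infer that the background warns of early water gains in particular. It speaks of water retention without tying it to the first weeks, and total body water is measured at weeks 0, 2 and 14. Nor is any use of week 2 as a covariate planned, since the listed tests have no covariates.

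What the reply does not remove is the contradiction itself. It is in the protocol's wording, so it is more than a detail deferred to a SAP, and the analysis section does not resolve it. Measuring body water helps to interpret lean mass, but it does not settle which change tests Aim 2.

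**Conclusion.** The point holds as an inconsistency with a conditional consequence. Baseline is week 0 in most of the protocol and a period ending at on-treatment week 2 in item 5(f). The change to be tested for Aim 2 is therefore open.

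If week 0 to 14 were chosen, a persisting pre-training effect would be significant in about 6% to 79% of trials for early effects of 0.1 to 0.9 SD, against about 5% for week 2 to 14. These rates rest on assumed effects, two-sided 5%, all 20 subjects per arm analysed, and an effect that neither grows nor fades after week 2.

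The week 2 to 14 contrast has its own limit. There is no untrained arm, creatine continues through training, and Attachment 3 repeats the load in weeks 7–8 and 13–14. The contrast therefore cannot separate later creatine accrual or repeat loading from true augmentation of training.

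**What to change.** - Reserve the word baseline for week 0. In item 5(f), call week 2 the end of the supplementation-only (pre-training) period.
- Define Aim 1 as the arm difference at week 2, adjusted for the week 0 value.
- Define Aim 2 as the arm difference in week 2 to week 14 change, with the week 0 value as covariate.
- Also report the week 0 to 14 arm difference, described as the combined effect of creatine with training versus placebo with training.
- State that, without an untrained arm, the Aim 2 contrast removes only what is already present at week 2.

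No new measurements are needed; the change is to wording and analysis specification. The real cost is power when part of the benefit appears before training, as in the 41% versus 79% example above. Activity and food intake have no week 2 measurement, so only the week 0 to 14 comparison is possible for them.
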